
### Sample Size and Power Analysis

A sample size calculation was performed using Stata V.16 (StataCorp), with the function “power two means cluster,” factored in 6 clusters (3 intervention neighborhoods and 3 control neighborhoods), and a 5% 2-sided alpha, as well as an assumed control average daily value of moderate-to-vigorous physical activity of 53.7 minutes, a SD of 19.7, and an intracluster correlation (ICC) value of 0.007, which was conservatively rounded up to 0.01. As the JU:MP project is a neighborhood/community-level intervention and no previous studies using accelerometry as an outcome assessment among children or young people could be identified, the values of average daily moderate-to-vigorous physical activity, SD, and ICC were derived from an unpublished pilot study (sample size n=564; 3 neighborhoods; 12 primary schools). The missingness of data was conservatively factored into the sample size calculation by assuming 30% accelerometer noncompliance at baseline, followed by further 50% loss of data (30% accelerometer noncompliance and 20% attrition) at both the 24-month and 36-month follow-ups. The parameters outlined led to a minimum recommended sample of 1200 children (600 per condition, 200 per neighborhood, and 32 per school) for adequate power (80%) to detect a change of at least 10 minutes in the primary outcome of average daily minutes of moderate-to-vigorous physical activity at both the 24-month and 36-month follow-ups.

### Data Analysis

Data will be entered electronically with a double data entry protocol using REDCAP software. Data will be kept on a secure file storage system, which will also be password protected. Data will be anonymized by the assignment of a unique identification number (study ID) to each participant. The primary comparative analysis (objective 1) will be performed on an intention-to-treat basis, including all participants recruited and without imputation for missing data. Multivariable mixed effects linear regression will be used to estimate differences in the primary outcome (accelerometer-assessed mean daily minutes of moderate-to-vigorous physical activity) between the intervention and control groups. Demographic variables of gender and ethnicity will be treated as random effect variables, and baseline moderate-to-vigorous physical activity, age, accelerometer wear time, BMI z-score, school, neighborhood, and condition will be treated as fixed effect variables. Similar analyses will be repeated for secondary outcomes (objective 2). A sensitivity analysis, using a suitable imputation method, will be conducted to assess the effect of missing data. *P* values and 95% CIs will be calculated. A small number of prespecified subgroup analyses will be carried out to evaluate whether the intervention is differentially effective in different subgroups, such as by neighborhood and school (objective 3). The trial is not powered to detect effectiveness in subgroups, and this analysis will be treated as exploratory, presented using CIs, and interpreted with caution. Mediation analysis using structural equation modeling will be applied to look at whether any intervention effect is mediated by potential determinants (objective 4), including (1) home physical activity, (2) school physical activity, (3) children’s sedentary screen time behaviors, (4) travel and street physical activity, (5) parent practices (nondirective support and autonomy support), (6) neighborhood social cohesion, (7) neighborhood walking/exercise environment, (8) religious setting physical activity, (9) physical activity during sports and recreation, and (10) park/green space physical activity, which the JU:MP program could have impacted based on the complexity of the program. Multimedia Appendix 2, Multimedia Appendix 3, and Multimedia Appendix 4 present 3 directed acyclic graphs that show the simple mediating pathways to be examined, the potential causal pathways between meditating variables, and the potential casual pathways between confounders (sex, ethnicity, age, socioeconomic status, and weight status), respectively.

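### With three neighborhoods per arm the condition effect has only about 4 degrees of freedom, but the stated model neither carries between-neighborhood variance nor refers the test to the neighborhood level

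*Protocol article*

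**What the plan says.** Protocol article, Sample Size and Power Analysis: the calculation "factored in 6 clusters (3 intervention neighborhoods and 3 control neighborhoods), and a 5% 2-sided alpha". It uses an SD of 19.7 minutes and an "intracluster correlation (ICC) value of 0.007, which was conservatively rounded up to 0.01". The result is "a minimum recommended sample of 1200 children (600 per condition, 200 per neighborhood, and 32 per school"), said to give "adequate power (80%) to detect a change of at least 10 minutes in the primary outcome" at both follow-ups.

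Protocol article, Data Analysis: "Multivariable mixed effects linear regression will be used to estimate differences in the primary outcome" between the arms. Gender and ethnicity are the random effects. School, neighborhood and condition are fixed, along with baseline activity, age, wear time and BMI z-score. P "values and 95% CIs will be calculated". The section names no estimator (ML or REML) and no degrees-of-freedom method. Similar analyses are planned for the secondary outcomes.

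**The concern.** The design section and the analysis section treat the neighborhood differently. For power, it is the unit that limits information: six clusters with a non-zero ICC. In the model as listed, no term puts between-neighborhood variance into the standard error of the condition effect, and nothing limits the reference distribution to what six neighborhoods can support.

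A child-level standard error treats the children in a neighborhood as independent and is too small. Making neighborhood a random effect repairs the variance, but that variance is then estimated from six units, and a multiplier of 1.96 is still too small. Either way the two-sided 5% test rejects too often and the 95% intervals cover too little. This affects the 24- and 36-month primary comparisons and the secondary outcomes analysed the same way. The trial could report the program as effective on evidence that six neighborhoods do not supply.

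**Working it through.** **Inputs from the protocol (Sample Size and Power Analysis).** Six neighborhoods, 3 per arm; two-sided alpha 5%; SD 19.7; ICC 0.007, rounded up to 0.01; difference 10 minutes; 200 children per neighborhood. Data loss is 30% at baseline, then a further 50% at both follow-ups. Analysed children per neighborhood, m:
- 50% loss counted once: 200 × 0.70 × 0.50 = 70
- 50% loss applied at each follow-up in turn: 70 × 0.50 = 35

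**Assumptions.** Equal neighborhood sizes, no separate school variance and no covariate adjustment. ICC 0.03 is an assumed value, used only to show sensitivity.

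**The plan's own figure.** With design effect 1 + (m − 1) × ICC, ICC 0.01 and a normal reference, 80% power needs m = 26, or 156 analysed. That is 446 recruited at 35% retention or 892 at 17.5%. With t on 4 df it needs m = 58, or 348 analysed: 995 or 1989 recruited. The stated 1200 was not reproduced at ICC 0.01 with either retention figure. The point here does not depend on it.

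**Degrees of freedom.** Condition is constant within a neighborhood, so the contrast has 6 − 2 = 4 df. The two-sided 5% critical value is 2.776 on 4 df, against 1.960 for the normal.

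**Model as listed.** Intercept plus neighborhood indicators has rank 6. Adding condition leaves it at 6, so condition cannot be estimated beside fixed neighborhoods; the same holds with fixed schools. Some change is therefore unavoidable, and the false-positive rate depends on which change is made.

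**(a) Arm contrast obtained, neighborhood variance left out of the SE.** Rate = 2 × [1 − Φ(1.96 / √(1 + (m − 1) × ICC))].
- ICC 0.007, m = 35: √1.238 = 1.113; 1.96/1.113 = 1.76; rate 7.8%
- ICC 0.007, m = 70: √1.483 = 1.218; 1.96/1.218 = 1.61; rate 10.8%
- ICC 0.01, m = 35: √1.34 = 1.158; 1.96/1.158 = 1.69; rate 9.0%
- ICC 0.01, m = 70: √1.69 = 1.300; 1.96/1.300 = 1.51; rate 13.2%

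**(b) Random neighborhood, normal reference, against neighborhood means on 4 df.** Simulated balanced null trials (at least 400,000 per setting), with the neighborhood variance bounded at zero:

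| ICC | m | REML, normal | ML, normal | Neighborhood means, t on 4 df |
|---|---|---|---|---|
| 0 | 35–70 | 3.8–3.9% | 4.6–4.8% | 5.0% |
| 0.007 | 35 | 5.4% | 6.9% | 5.0% |
| 0.007 | 70 | 6.6% | 8.7% | 5.0% |
| 0.01 | 35 | 6.0% | 7.8% | 5.0% |
| 0.01 | 70 | 7.5% | 10.1% | 5.0% |
| 0.03 (assumed) | 35 | 8.7% | 12.0% | 5.0% |
| 0.03 (assumed) | 70 | 10.4% | 15.1% | 5.0% |

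**Interval width.** At ICC 0.01 and m = 70, SE = 19.7 × √(1.69 × 2 / (3 × 70)) = 2.50. Half-width: 1.960 × 2.50 = 4.9 minutes, against 2.776 × 2.50 = 6.9. Ratio 2.776/1.960 = 1.42.

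**Power for 10 minutes, ICC 0.01.**
- m = 70: 10/2.50 = 4.00; 84% on 4 df (97.9% with a normal reference)
- m = 35: SE = 19.7 × √(1.34 × 2 / (3 × 35)) = 3.15; 10/3.15 = 3.18; 67% on 4 df (88.8% with a normal reference)

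**The case against.** The strongest reply is that the protocol never says it will use a normal reference. Estimator and degrees-of-freedom method are details usually left to an analysis plan, which is not shown. That stands as far as it goes: silence on the method is not in itself an error. But the section is not silent on the model. It sorts the terms into fixed and random, and that list leaves between-neighborhood variance out, against a power calculation built on six neighborhoods. A reader cannot get from the stated model to a neighborhood-level test without changing it.

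A second reply is that the prior defect is fixed neighborhood and school beside condition, so the simulated random-neighborhood model is not the one written. This is correct. The rates under (b) describe what happens if that defect is repaired in the obvious way and nothing more is done. The rates under (a) describe a fit in which the arm contrast is recovered but the standard error stays at child level.

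A reader might also infer a general false-positive rate as high as 16%. The documents do not support that. Among random-neighborhood fits, a rate near that level needs ML together with an ICC of about 0.03, three times the plan's rounded-up value. With REML at the plan's ICC, the rate is only 5.4–7.5%.

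**Conclusion.** The concern holds in a limited form. The stated analysis does not carry the six-neighborhood structure of the power calculation into the test of condition. At the protocol's ICC of 0.007–0.01 and 35–70 analysed per neighborhood, the 5% test would run at about 8–13% with neighborhood variance omitted. With a random neighborhood and a normal reference it would run at about 5–8% (REML) or 7–10% (ML). If the ICC were 0.03, the latter two become about 9–10% and 12–15%.

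These figures rest on balanced clusters and come from formula or simulation; none is stated in the protocol. At ICC zero there is no inflation. It would go too far to say that the protocol commits itself to large-sample inference, or that one inflation figure applies whatever the estimator, ICC and cluster size. Because the primary comparison at both timepoints is affected and the protocol reports that analysis has not begun, the change should be made now.

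**What to change.** In Data Analysis, remove neighborhood and school as fixed effects beside condition. State that the condition effect and its 95% CI rest on neighborhood-level inference: preferably, compare the six covariate-adjusted neighborhood means by a t test on 4 df (critical value 2.776). This form, without covariates, held 5.0% in every setting simulated.

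REML with random neighborhood and Kenward-Roger degrees of freedom is an alternative, but it was not simulated here. It may be conservative when the neighborhood variance is estimated at zero, which happened in about 33% of null trials at ICC 0.01 and m = 70. A rough analogue, bounded REML with 4 df imposed throughout, rejected in only 1.6% of trials there and 1.0% at m = 35. If this route is taken, say in advance that a zero estimate does not lead to dropping the neighborhood term or returning to child-level degrees of freedom. A permutation test cannot substitute: 3 versus 3 gives 20 allocations, so the smallest two-sided P is 2/20 = 0.10.

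The cost is a few sentences of wording and no new data, but a CI multiplier 1.42 times larger. Power on 4 df is about 84% or about 67% according to how the 50% loss is read, so the protocol should state which reading it intends alongside the power figure.

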### Aims and Objectives

The aim of this quasiexperimental trial is to explore whether JU:MP is effective at increasing physical activity among children aged 5 to 11 years. The specific research objectives are as follows:

Determine the effectiveness of JU:MP to increase device-measured (accelerometry) mean average daily moderate-to-vigorous physical activity among children aged 5 to 11 years 24 months and 36 months after the implementation of a whole-system community intervention.Determine the effectiveness of JU:MP to improve secondary outcomes among children aged 5 to 11 years 24 months and 36 months after the implementation of a whole-system community intervention. The secondary outcomes are as follows: (1) mean average daily, weekday, and weekend day sedentary time (device measured [accelerometry]); (2) mean average daily, weekday, and weekend day light physical activity (device measured [accelerometry]); (3) weight status and body fat level (waist circumference and BMI); (4) socioemotional well-being, including prosocial behavior, emotional problems, behavioral problems, peer problems, and hyperactivity/inattention (teacher reported); and (5) children’s quality of life (parental reported).Undertake exploratory subgroup analysis (ie, neighborhood level and school level) investigating the change in the primary and secondary outcomes.Investigate the potential meditating effects of changes in contextual factors (JU:MP is seeking to change; parental reported): (1) home physical activity, (2) school time physical activity, (3) children’s sedentary screen time behaviors, (4) active travel and street physical activity, (5) parent practices (nondirective support and autonomy support), (6) neighborhood social cohesion, (7) neighborhood walking/exercise environment, (8) religious setting physical activity, (9) physical activity during sports and recreation, and (10) park/green space physical activity.

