### Identification of Neighborhoods

The JU:MP program is operating in 8 distinct neighborhoods. The 3 neighborhoods eligible for participation in this effectiveness trial are the 3 direct-delivery neighborhoods of JU:MP. Control neighborhoods will be based on local authority wards (local areas with elected officials representing the local area) and be in the county of West Yorkshire in order to ensure that neighborhoods would be politically and geographically similar to the JU:MP neighborhoods. Other neighborhoods/wards in Bradford have been excluded due to potential intervention contamination. Control neighborhoods must ideally have similar characteristics to the JU:MP neighborhoods to maximize internal validity. The process of identifying control neighborhoods will include pooling state-funded primary school census data [33], which are released from schools annually, for every ward in West Yorkshire and then calculating the median/mean of (1) the value of the school postcode-derived IMD (IMD 2019) [34]; (2) the proportion of children eligible for state-funded free school meals (school population measure of deprivation); and (3) the proportions of the 2 predominant ethnic groups in the 3 JU:MP areas (White British and South Asian heritage [combining Pakistani heritage, Bangladesh, Indian, and other South Asian ethnic groups]). Ward areas deemed to be suitable control areas must have no more than 1 IMD decile median difference than a JU:MP neighborhood and no more than 10% difference in the proportion of children eligible for free school meals, and the predominant ethnic group (majority or large minority) must be the same as that in a JU:MP neighborhood with ideally no more than 15% difference.

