### Recruitment of Schools

Once the neighborhoods are selected, government-funded primary schools located in the JU:MP and control neighborhoods will be invited to participate in the research. The number of control schools recruited will be dependent on the recruitment of intervention schools in the neighborhoods to the study. Private and designated special schools have been excluded from this study. Identified schools will be contacted via standardized emails and follow-up phone calls (48 hours later) to request and arrange an in-person/virtual meeting to discuss the study and school-level consent. The primary schools in the JU:MP neighborhoods will be part of the JU:MP program and will receive whatever benefits may be derived from participating in the program. The primary schools within the control areas will not be offered access to the JU:MP program and must agree in principle not to commit to any whole-system school physical activity research in the next 3 years. To incentivize such a commitment, each of the primary schools in the control areas will be offered a total of £600 (US $727), with the caveat that this should not be spent on physical activity provision (physical education, active travel, after school clubs, etc) for the duration of the 3-year study. The £600 (US $727) payment will be split into 3 instalments of £200 (US $242) to be paid after the competition of each of the 3 study data collections (baseline, 24-month follow-up, and 36-month follow-up). If the school agrees to participate in the study, arrangements will be made to begin recruiting children.

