## Results

This study has been registered at ISRCTN (ISRCTN14332797). Recruitment occurred from July 2021 to March 2022, and baseline data collection occurred from September 2021 to March 2022. As of March 2022 (end of baseline data collection), a total of 1454 children from 37 schools (17 intervention schools and 20 control schools) have been recruited. The first follow-up data collection will occur from September 2023 to March 2024, and the second and final follow-up data collection will occur from September 2024 to March 2025. Data analysis has not begun, and the final results will be published in December 2025.

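### Differential effectiveness by neighborhood and by school cannot be tested, because every neighborhood and every school contains only one arm

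*Protocol article*

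**What the plan says.** In the protocol article, the third objective (Aims and Objectives) is "Undertake exploratory subgroup analysis (ie, neighborhood level and school level"), looking at change in the primary and secondary outcomes. Data Analysis gives the purpose: a small number of prespecified subgroup analyses "to evaluate whether the intervention is differentially effective in different subgroups, such as by neighborhood and school (objective 3"). The same section says that the trial is not powered for subgroups, and that these analyses are exploratory, shown with confidence intervals and to be read cautiously.

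Four other places fix how arm relates to neighborhood and school:

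- Sample Size and Power Analysis: the calculation "factored in 6 clusters (3 intervention neighborhoods and 3 control neighborhoods), and a 5% 2-sided alpha".
- Recruitment of Schools: "The primary schools in the JU:MP neighborhoods will be part of the JU:MP program", whereas "The primary schools within the control areas will not be offered access to the JU:MP program".
- Identification of Neighborhoods: "Other neighborhoods/wards in Bradford have been excluded due to potential intervention contamination". A suitable control ward "must have no more than 1 IMD decile median difference than a JU:MP neighborhood", with similar limits for free school meals and ethnicity. No one-to-one pairing is recorded.
- Results: "a total of 1454 children from 37 schools (17 intervention schools and 20 control schools) have been recruited".

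For the model, Data Analysis lists school, neighborhood and condition as fixed effects. It defines no matched-set factor, and no comparator for a single neighborhood or school.

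**The concern.** To say that an intervention works better in one subgroup than in another, one needs a treated-versus-control contrast inside each subgroup and then a comparison of those contrasts. If a subgroup level holds only one arm, it has no such contrast. What remains is the change observed there, which mixes any program effect with ageing, local trend and chance.

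This is a failure of identification, not of precision. The stated safeguards (exploratory status, confidence intervals, caution) address imprecision only. An interval around a quantity that is not an intervention effect is still not an interval for an intervention effect. At stake is whether the third objective, as worded, can say anything about where the program was more or less effective.

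**Working it through.** **The plan's own figure.** The protocol gives no figure for the subgroup analyses. Its overall target is 1200 children, 600 per arm and 200 per neighborhood (1200 / 6 = 200). With 30% loss at baseline and a further 50% at follow-up, 200 × 0.7 × 0.5 = 70 analysed per neighborhood. The calculation does not return exactly 1200 under the readings of the loss that were tried, but nothing below depends on that.

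**Step 1: units holding both arms.** From the sections cited, all schools in the 3 JU:MP neighborhoods are intervention and all schools in the 3 control neighborhoods are control. Neighborhoods with both arms: 0 of 6. Schools with both arms: 0 of 37 (17 + 20).

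**Step 2: estimability.** Let D_g be the indicator of neighborhood g, and a_g its arm (1 or 0).

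- Arm = Σ a_g D_g, a combination of columns already present.
- Arm × D_g = a_g D_g, which is either D_g itself or zero.

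Neither adds information. Numerically:

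| Design | Columns | Rank |
|---|---|---|
| Intercept + neighborhood | 6 | 6 |
| + arm + arm × neighborhood | 12 | 6 |
| Intercept + school | 37 | 37 |
| + arm + arm × school | 74 | 37 |

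The numerical check assumed a split of schools over neighborhoods (6/6/5 and 7/7/6). The rank does not depend on it.

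**Step 3: what a neighborhood contrast could offer.** Inputs from Sample Size and Power Analysis: SD 19.7, ICC 0.01, and 70 analysed per neighborhood as above. The variance of one neighborhood mean is

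v = 19.7² × (0.01 + 0.99/70) = 388.09 × 0.02414 = 9.37.

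- One JU:MP neighborhood against one control neighborhood: SE = √(2v) = √18.74 = 4.33 min. With z, ±8.5 min. If v must be estimated from 6 neighborhood means in 2 arms (4 df, t = 2.776), ±12.0 min.
- One JU:MP neighborhood against the 3 pooled controls: SE = √(v × 4/3) = 3.53 min.
- Difference between two one-to-one contrasts, which is what differential effectiveness would need: SE = √(4v) = 6.12 min, or ±12.0 min even with z.
- Difference between two contrasts that share the pooled controls: the controls cancel, leaving one JU:MP neighborhood against another, SE = √(2v) = 4.33 min. This comparison contains no control information.

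If the 50% loss is applied at each follow-up in turn, 35 remain per neighborhood, and the one-to-one SEs become 5.45 and 7.71 min. These figures use the unadjusted SD. Adjustment for baseline would reduce them by an amount that the document does not allow one to compute.

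**Step 4: would a condition-by-matched-set test rescue it?** Assume three pairs. The term is estimable (rank 6 of 6 columns), but each cell holds one neighborhood, so there are 0 degrees of freedom for variation between neighborhoods. If children are treated as independent, the 2-df test statistic is inflated by the ratio of v to its within-neighborhood part:

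- ICC 0.01: 0.02414 / 0.01414 = 1.707. P(χ²₂ > 5.991/1.707) = exp(−1.755) = 0.17.
- ICC 0.007: 0.02119 / 0.01419 = 1.493. P(χ²₂ > 5.991/1.493) = exp(−2.006) = 0.13.

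Simulation gave 0.172 and 0.134. A nominal 5% test would thus reject in 13% to 17% of trials with no true difference.

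**The case against.** The protocol never writes down an interaction term. A JU:MP neighborhood can be compared with similar control wards or with all controls, and that contrast is estimable if the areas are assumed comparable. This stands: for neighborhoods, the defect is an undefined comparator and no replication at area level. It does not help the school level, where no comparator is suggested at all.

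The analysis is declared exploratory and underpowered. That is fair, and it limits the weight of the point. But the declaration concerns precision, and the problem is that the named quantity does not exist within these units.

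A reader might infer three stronger things that the document does not support:

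- *That schools or neighborhoods will be ranked on uncontrolled change.* No section plans a ranking. The objective speaks loosely of change, but Data Analysis frames the aim as effectiveness of the intervention.
- *That no child-level modifier is planned.* The wording in Data Analysis (*such as*) leaves the list open, although the objective (*ie*) reads narrower. A condensed article may leave the full list to an analysis plan that is not shown.
- *That subgroup effects in general cannot be studied.* The problem reaches only factors on which each level contains a single arm.

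**Conclusion.** The point holds for the two factors that the protocol names. With 0 of 6 neighborhoods and 0 of 37 schools containing both arms, condition-by-neighborhood and condition-by-school effects are not identified, whatever the sample size. Neighborhood-specific contrasts survive only as descriptive results under a comparability assumption. The difference between two one-to-one contrasts is uncertain by about ±12 minutes, which exceeds the 10-minute effect for which the trial is sized.

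The structural conclusion rests only on the allocation described in the protocol. The sizes rest on its planning SD and ICC, on 70 analysed children per neighborhood, and on 3 control neighborhoods as in the sample size section. It would be too strong to say that the third objective cannot be pursued in any form: it can, with a stated comparator or with other modifiers. For an exploratory objective this should be corrected, but it does not by itself threaten the primary comparison. The same nesting makes condition collinear with the fixed school and neighborhood terms in the primary model; that is a separate matter.

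**What to change.** 1. Remove school as a subgroup factor for differential effectiveness. Report school-level results only as descriptive variation. A between-school variance would require school to be modelled as a random effect, which Data Analysis does not do at present.
2. For neighborhoods, state the comparator: either the control wards that met the matching criteria for that JU:MP neighborhood, or the pooled controls. Present the contrasts as descriptive, with intervals and without an interaction test. Say that differences between contrasts sharing the pooled controls are only differences between JU:MP neighborhoods.
3. Base any exploratory test of differential effectiveness on characteristics recorded for children in both arms, as condition-by-characteristic terms. Sex, ethnicity and free school meals are already requested from schools (Child Demographics and Anthropometric Data). The characteristic needs its own fixed main effect in that model; free school meals is not in the listed model, and gender and ethnicity are listed there as random effects.

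The cost is small edits to the objective and the subgroup model, and a written record of which control wards match which neighborhood. No new data are needed. The protocol states that analysis has not begun, so the change can still be prespecified.
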